## Abstract

**Background:**

BIPCOM aims to (1) identify medical comorbidities in people with bipolar disorder (BD); (2) examine risk factors and clinical profiles of Medical Comorbidities (MC) in this clinical group, with a special focus on Metabolic Syndrome (MetS); (3) develop a Clinical Support Tool (CST) for the personalized management of BD and medical comorbidities.

**Methods:**

The BIPCOM project aims to investigate MC, specifically MetS, in individuals with BD using various approaches. Initially, prevalence rates, characteristics, genetic and non-genetic risk factors, and the natural progression of MetS among individuals with BD will be assessed by analysing Nordic registers, biobanks, and existing patient datasets from 11 European recruiting centres across 5 countries. Subsequently, a clinical study involving 400 participants from these sites will be conducted to examine the clinical profiles and incidence of specific MetS risk factors over 1 year. Baseline assessments, 1-year follow-ups, biomarker analyses, and physical activity measurements with wearable biosensors, and focus groups will be performed. Using this comprehensive data, a CST will be developed to enhance the prevention, early detection, and personalized treatment of MC in BD, by incorporating clinical, biological, sex and genetic information. This protocol will highlight the study's methodology.

**Discussion:**

BIPCOM's data collection will pave the way for tailored treatment and prevention approaches for individuals with BD. This approach has the potential to generate significant healthcare savings by preventing complications, hospitalizations, and emergency visits related to comorbidities and cardiovascular risks in BD. BIPCOM's data collection will enhance BD patient care through personalized strategies, resulting in improved quality of life and reduced costly interventions. The findings of the study will contribute to a better understanding of the relationship between medical comorbidities and BD, enabling accurate prediction and effective management of MetS and cardiovascular diseases.

*Trial registration*: ISRCTN68010602 at https://www.isrctn.com/ISRCTN68010602. Registration date: 18/04/2023.

**Supplementary Information:**

The online version contains supplementary material available at 10.1186/s40345-024-00337-8.

## Background

Bipolar Disorder (BD) is a severe, complex genetic disorder with a wide range of clinical presentations and a multifactorial etiology (Grande et al. 2016). It ranks as the 6th highest disease burden worldwide and contributes significantly to the global economic burden. BD is a critical public health concern due to its high prevalence (more than 1% of the world's population), chronic nature, high disability rate, and association with both psychiatric and Medical Comorbidities (MC) (Grande et al. 2016). Patients with BD have an elevated risk of cardiovascular disease (CVD) mortality, resulting in a reduced life expectancy of 10–20 years (Miller and Bauer 2014; Laursen 2011; Roshanaei-Moghaddam and Katon 2009), primarily due to a high level of MC in this population (Roshanaei-Moghaddam and Katon 2009), such as type 2 diabetes, CVD, musculoskeletal disorders, renal disorders, neurological disorders, and metabolic syndrome (MetS) (McIntyre et al. 2007). The heightened cardiovascular mortality in individuals with BD is possibly due to multiple factors. Medications like lithium and valproic acid may lead to weight gain and disrupt glucose metabolism, while second-generation antipsychotics are linked to hyperlipidaemia, insulin resistance, and weight gain (Weiner et al. 2011), nonetheless, despite these associations, long-term treatment with antipsychotic drugs has been correlated with lower mortality rates when compared to individuals who do not use antipsychotics (Tiihonen et al. 2009). Lifestyle factors such as poor diet, inadequate exercise, and higher rates of smoking further compound these risks. As a result, common cardiovascular risk factors like obesity, hypertension, diabetes, and hyperlipidemia are more prevalent among those with BD, amplifying their susceptibility to cardiovascular mortality (Weiner et al. 2011; Swartz and Fagiolini 2012). In addition, MC in BD are associated with unfavourable medical outcomes of this mental disorder such as treatment resistance, mood relapse or cognitive disorders (Bauer et al. 2018). Factors contributing to these higher MC rates in BD include pathogenic links between a variety of risk factors such as pathogenic and biological factors (e.g., metabolic, or immune system disorders, genetic susceptibility), medication exposure, unhealthy lifestyles, underutilization of health services, and co-occurring mental disorders (Keck and McElroy 2003; Carney and Jones 2006; Chengappa et al. 2000; Liese et al. 1998). Furthermore, the interplay of genetic susceptibility and underlying physiological processes, including heightened activation of immunometabolic or endocrine systems in both central and peripheral contexts, contributes to the development of both MetS and psychiatric disorders (Penninx and Lange 2018). MetS is a complex and multifaceted medical condition characterized by a cluster of interconnected risk factors that significantly increase the risk of heart disease, stroke, and type 2 diabetes. These risk factors often occur together and share common underlying mechanisms (Eckel et al. 2005). While there is no single universally accepted definition of MetS, several major health organizations and expert groups have agreed on three out of the five criteria listed in Table 1 required to fulfill a diagnosis of MetS (Alberti et al. 2009). The MetS is significantly more prevalent (by 1.98 times) in patients with BD than in the general population (Vancampfort et al. 2013; Godin et al. 2024; Godin et al. 2014). This high prevalence rate is plausibly explained by a range of multiple factors, including medication side effects, unhealthy lifestyles, and pathogenic and biological factors (Firth et al. 2020). For example, certain antipsychotic medications are associated with weight gain and insulin resistance, which in turn increase the risk of developing MetS. In addition, people with BD experience periodic mood fluctuations that affect their ability to maintain a healthy lifestyle (Penninx and Lange 2018). Physical activity (PA) and sleep patterns play important roles in MetS development. MetS is positively associated with physical inactivity and sedentary behaviour, while healthy sleep patterns benefit cardiometabolic health (Amirfaiz and Shahril 2019; Huang and Redline 2019). It is proven that patients with BD are typically less active, more sedentary, and experience poorer sleep quality (Janney et al. 2014; Brochard et al. 2018). Despite the high MC prevalence in BD, patients often receive inadequate diagnoses and treatment, and comprehensive studies on this topic remain limited, hindering personalized plans and preventive treatments. Neglecting comorbidities in BD management creates relevant obstacles to early and effective interventions for patients. For all these reasons, collaborative efforts between mental health and medical services are essential to enhance diagnosis and treatment, improve quality of life, and reduce comorbidity-related mortality in patients with BD.

**Table 1 Tab1:** Diagnostic criteria for MetS as agreed in the Consensus Statement published in Alberti et al., 2009

Diagnostic criteria	Threshold values
Waist circumference	≥ 102 cm (M); ≥ 88 cm (F)
Fasting plasma glucose	≥ 100 mg/dL or specific treatment
Blood pressure	≥ 130/85 mmHg or specific treatment
Triglycerides	≥ 150 mg/dL or specific treatment
HDL cholesterol	< 40 mg/dL (M); < 50 mg/dL (F) or specific treatment

## Methods

### Aims

The BIPCOM project aims to enhance personalized treatment for comorbid medical conditions, including MetS, in individuals with BD. The project's objectives include: (1) identifying MetS prevalence and risk factors in patients with BD using Nordic registries, biobanks, and medical records; (2) conducting an exploratory clinical study (ECS) with 400 subjects recruited from 11 centres to study the clinical profile and 1-year incidence of MetS; and (3) developing a Clinical Support Tool (CST) that utilizes clinical, biological, and genetic data to enhance personalized treatment for comorbidities, including MetS, with consideration for sex differences. MetS in patients with BD serves as a 'pilot case' due to its implications for prevention and precision medicine (PM). The project aims to pioneer PM approaches in BD, leading to innovative, individualized care models for implementation in clinical practice (Kupfer 2005): these efforts seek to improve healthcare delivery, patient stratification, disease prediction, and prevention, ultimately enhancing patient care and outcomes.

### The general architecture of the project

The BIPCOM project will combine various methods and approaches. These include a register study, a survey of medical records, and the ECS incorporating the use of actigraphy and Experience Sampling Method (ESM). ESM, an ecologically valid method, provides a comprehensive view of daily life, assessing various constructs like quality of life and psychopathology and psychological mechanisms such as stress-sensitivity and coping. These constructs are challenging to obtain through traditional cross-sectional questionnaires. ESM finds applications in treatment monitoring, ecological momentary interventions, clinical trials, and single-case clinical assessments. Data collection can be simplified using a smartphone app (Verhagen et al. 2016). The project will also include a qualitative study with focus groups to assess the multiple dimensions of MC, seen from the ‘eyes’ of patients, clinicians, and family members.

This comprehensive approach will culminate in the development of a CST that will prove valuable to a diverse range of professionals. The BIPCOM project will last 3 years, but the clinical study will take place over a period of approximately 1 year. In the following sections, we will describe all the components of the project.

### Study design

#### Study 1: the registry study

The consortium, drawing on extensive genetic epidemiology expertise, will leverage Swedish and Norwegian national registers and biobanks with (single-nucleotide polymorphism) SNP-array genotyped samples. It will begin by identifying adult Swedish residents from the Swedish National Patient Register and the Swedish Prescribed Drug Register, with registered treatment contact for BD. A similar process will be implemented with Norwegian registers. Subsequently, the consortium will investigate diagnosed MC, comparing individuals with and without BD. The primary focus of the Swedish and Norwegian teams is to explore the associations between BD onset and MC risk, with a specific emphasis on MetS. Additionally, it will include type 2 diabetes and CVD as relevant outcome variables due to their strong association with MetS. Research outcomes will be determined using a combination of diagnostic data from patient registers and pharmacological treatment details from the prescribed drug register, as shown in Table 2. Furthermore, risk prediction models for cardiometabolic conditions in individuals with BD will be developed, with CVD and type 2 diabetes as primary outcomes, and MetS, and all-cause and cause-specific mortality, as secondary outcomes. Given the absence of complete MetS diagnostic criteria in Swedish population registries, the consortium will use several related medical conditions as proxies (e.g., obesity, hypertension, hyper/dyslipidaemia). Access to genotyping data from approximately 1.3 million participants, derived from Illumina arrays or similar platforms in existing genotyped cohorts, will further enrich the study.

**Table 2 Tab2:** Socio-demographic and clinical characteristics to be used for the training set with the Swedish registry

1	Sex
2	Ethnicity
3	Age
4	Marital status
5	Children (yes/no)
6	Education years, Mean (SD)
7	Area of residence (urban/rural)
8	Current occupational status
9	Poverty (poor housing, malnutrition, etc.)
10	Age of first contact with mental health services (Years), Mean (SD)
11	Bipolar disorder I or II
12	Comorbidity with other mental disorders
13	Number of lifetime psychiatric hospitalizations
14	The overall length of psychiatric hospitalizations (months)
15	Lifetime substance or alcohol use disorder (yes/no)
16	Ever treated with lithium or mood stabilizers
17	Ever treated with antipsychotics
18	Number of diagnoses of MC lifetime
19	Number of lifetime hospitalizations in any medical wards
20	Body Mass Index (BMI)
21	Information about all drug prescriptions in the lifetime
22	Smoking (yes/no)
23	Sleep problems
24	Familiarity with diabetes and/or CVD

While leveraging national registers offers significant advantages, several limitations will have to be considered when interpreting findings from this study. First, the reliance on proxy conditions to represent MetS may introduce potential misclassification bias. The absence of complete diagnostic data in the registries limits the study's ability to accurately capture the true prevalence of MetS among individuals with BD. Additionally, individual proxies might not fully capture the complex interplay of factors contributing to MetS, potentially underestimating the true association between MetS and these outcomes in BD. Second, the study is inherently limited to information available in the registers, which may lack granularity around certain lifestyle factors, clinical metrics, and disease progression markers over time. Lastly, the utilization of specific-cause mortality outcomes should also be interpreted with caution due to potential discrepancies between recorded and actual causes of death (Brooke et al. 2017).

#### Study 2: the study of medical records

BIPCOM offers a unique opportunity to gather and analyse extensive datasets from patients with BD utilizing local medical services across five countries. All centres participating to this project use electronic patient records: an ad hoc Medical Record Abstraction Tool (MRAT) will be employed to extract clinical data and information related to 32 predefined variables (Additional file 1: Table S1), including past and current comorbidities and treatments, and a set of biomarkers related to MetS. Patients with BD will be randomly selected from those with inpatient or outpatient visits, aiming for a total sample size of at least 1,500 patients (300 per site). Rigorous measures will be taken to minimize selection bias and ensure data quality, following Jansen's guidelines (Jansen et al. 2005), which involve cross-verification with source documents, close collaboration with local physicians, written guidelines for data collectors, interobserver studies for training, regular data collector meetings, and random checks of completed MRATs against original medical records. Consent is not required as the data used are fully anonymized clinical routine data. MRAT will capture information on various medical comorbidities, including MetS, diabetes mellitus, dyslipidaemias, obesity, endocrine imbalances, CVD, other significant comorbidities, and concurrent prescribed drug use.

#### Study 3: the Exploratory Clinical Study (ECS)

##### Participants

Study 3 consists of the ECS conducted in five countries (France, Italy, Germany, Norway, and Spain), with a total of 11 recruiting sites (Additional file 1: Table S2). A total of 400 participants, aged 18–65 years, diagnosed with either BD I or BD II or BD not otherwise specified (NOS) according to the DSM-5, will be enrolled: these participants will be selected from patients with BD who have had at least one contact with the mental health service in the past year. Table 3 shows the inclusion and exclusion criteria. To ensure a representative sample of patients with BD, a specific stratification will be employed, according to the following schema: age will be split into two strata (18–45 and 46–65 years), sex will be split into two strata (male and female) and age of onset (before 21 years and after 21 years) will be used as a proxy of disorder severity.

**Table 3 Tab3:** Inclusion and exclusion criteria for the ECS

Inclusion criteria	Exclusion criteria
Age 18–65 years	Plan to relocate in the subsequent year
Primary diagnosis of BD I or BD II or BD NOS	Severe psychiatric comorbidities (schizophrenia spectrum disorders)
At least one contact with the mental health service in the last year	Severe cognitive impairment
Signed informed consent	Severe substance/alcohol misuse as quantified by specific scores on the Alcohol Use Disorders Identification Test (AUDIT) (Babor et al. 2001) and the Drug Abuse Screening Test (DAST) (Skinner 1982)

The study foresees 2 evaluation times: the first at the entry into the study (T0) and the second after 1 year (T1).

##### Recruitment strategy

A random selection of eligible patients will be conducted within each stratum. Considering an anticipated refusal rate of approximately 30%, we will screen 130 eligible patients per country; the Spanish site will screen about 50 patients and will recruit not more than 30 patients. Trained researchers will conduct assessments using the Structured Clinical Interview for DSM-5 (SCID-5)—Clinical Version, specifically focusing on the BD section, to confirm the BD diagnoses.

##### Participant retention strategies in study 3

Due to the characteristics of the study population group (people with BD, possibly of working age), we have allowed for a 20% dropout rate. To maximise response and participation in the ECS, we propose a reimbursement of transport costs for everyone who decides to participate to the study, based on the availability of funds and the permissions of each ethics committee. Participants may be contacted using several methods of communication (post/phone/email); contact details of all participants, including general practitioner (GP) and clinician details, will be recorded in a ‘keeping in touch’ form and each contact, or contact attempt, made with participants will be recorded in a bespoke contact log. All participants will remain in the study and follow-up data will be sought unless consent for participation in data collection is explicitly withdrawn.

##### Clinical measures

A "Patient Schedule" (PS) will be created to capture socio-demographic, clinical, and treatment-related data of each participant at baseline (T0) and during the 1-year follow-up (T1). Table 4 provides detailed information about all assessment instruments to be administered to participants at T0.

**Table 4 Tab4:** List of standardized assessment tools in the ECS

Name	Description	Item	Scoring range	Languages of the project in which it was validated
Structured Clinical Interview for DSM-5 (SCID-5)—Clinical Version (First 2014)	Structured clinical interview	Only the BD section		IT, FR, DE, NO, ESP
Alcohol Use Disorders Identification Test (AUDIT) (Babor et al. 2001)	Screening tool to assess alcohol consumption patterns and alcohol use disorders	10	0–40	IT, FR, DE, NO, ESP
Drug Abuse Screening Test (DAST) (Skinner 1982)	Self-report questionnaire to screen for substance use disorders	10	0–6 +	IT, FR, ESP
World Health Organization Disability Assessment Schedule 2.0, self-report version (WHODAS 2.0) (Ustün et al. 2010)	Tool to assess the impact of health conditions on functioning in six domains of life (cognition, mobility, self-care, getting by, activities of daily living, and participation)	12	0–100	IT, FR, DE, NO, ESP
Functioning Assessment Short Test (FAST) (Rosa et al. 2007)	Self-report questionnaire to assess functional impairment and disability in individuals with mental disorders	24	0–40 +	IT, FR, DE, NO, ESP
Elixhauser Comorbidity Index (ECI) (Fabbian et al. 2017)	System for classifying medical comorbidities according to ICD categories	NA	NA	IT, FR, DE, NO, ESP
EQ5D Health questionnaire (Rabin and Charro 2001)	Self-report tool to assess the quality of life focusing on 5 dimensions: mobility, self-care, usual activities, pain/discomfort, and anxiety/depression	5	0–100	IT, FR, DE, NO, ESP
Short Form Health Survey (SF-36) (Brazier et al. 1992)	Self-report tool to assess the quality of life covering eight health-related domains	36	0–100	IT, FR, DE, NO, ESP
Pittsburgh Sleep Quality Index (PSQI) (Buysse et al. 1989)	Self-report tool to assess sleep quality and structure in adults by measuring seven domains	19	0–21	IT, FR, DE, NO, ESP
Childhood Trauma Questionnaire (CTQ) (Bernstein et al. 1994)	Self-report tool used to assess childhood trauma experiences	28	5–125	IT, FR, DE, NO, ESP
Fagestrom scale (Heatherton et al. 1991)	Self-report tool used to assess nicotine dependence in individuals who smoke cigarettes	6	0–10	IT, FR, DE, NO, ESP
Mini-Mental State Examination (MMSE) (Folstein et al. 1975)	Screening tool used to assess cognitive impairment	11	0–30	IT, FR, DE, NO, ESP
Handgrip squeeze test (Sayer et al. 2006)	It measures the maximum isometric strength of the hand and forearm muscles			
Knee extension test (Bohannon 1986)	It measures the hamstring muscle length and the range of active knee extension in the position of hip flexion			

Assessments will be conducted through participants' illness history and BD treatments. A structured physical examination, based on the Physical Examination Essential Checklist (Additional file 1), will be administered, with any signs of ill health promptly reported to clinicians.

During the physical examination, patients will complete the Knee extension test (Bohannon 1986) and the handgrip squeeze test (Sayer et al. 2006) measured through a dynamometer. Additionally, clinical electrocardiograms (ECGs) will be performed to identify QTc prolongation or the presence of arrhythmias. The primary aim of the ECS is to identify common associations among the five MetS diagnostic criteria in patients with BD at both T0 and T1 using clustering techniques and multiple correspondence analyses. Each stratum within each site will include approximately 14 subjects, totaling approximately 57 patients from the 400-sample pool, ensuring data representativeness and statistical power. The 1-year follow-up phase will begin immediately after the baseline assessment. At the end of this period, participants will undergo reassessment using a set of tools (Additional file 1: Table S3) to evaluate the clinical progression or improvement in MetS criteria, focusing on changes among patients meeting these criteria.

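### The stated allocation in the exploratory clinical study (about 14 per stratum and 57 per site) does not fit 400 patients, 11 sites and the stated strata, and equal stratum numbers do not by themselves ensure representativeness

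*Protocol article*

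**What the plan says.** Study 3, Participants, sets the size and layout: "A total of 400 participants, aged 18–65 years", in five countries "with a total of 11 recruiting sites". To obtain a representative sample it stratifies by age (18–45 and 46–65 years) and by sex, and adds a third two-level factor: "age of onset (before 21 years and after 21 years) will be used as a proxy of disorder severity".

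Recruitment strategy selects eligible patients at random within each stratum. It expects about 30% to refuse, and for that reason states that "we will screen 130 eligible patients per country". The Spanish site is the exception: it screens about 50 and recruits no more than 30.

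Clinical measures then gives the allocation: "Each stratum within each site will include approximately 14 subjects, totaling approximately 57 patients from the 400-sample pool, ensuring data representativeness and statistical power".

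Under Data analyses, Study 3 plans to describe how the 32 possible combinations of the five MetS criteria are distributed among patients with bipolar disorder (BD). It also plans group comparisons, multistate models and multiple correspondence analysis.

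**The concern.** The allocation sentence gives sites their recruitment targets. If the targets do not agree with the total, the number of sites or the number of strata, sites cannot meet them, and the article does not say which figure gives way.

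The sentence also offers the allocation as the reason why the sample is representative and the study has power. Filling every stratum to about the same number is equal allocation. It reproduces the mix of patients in the services only where the strata are equally large there. Otherwise small strata are over-represented, and any unweighted description of the whole sample reflects the quota mix rather than the patient population.

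**Working it through.** **Inputs, all from Study 3.** N = 400; 11 sites; three binary factors, so 2 × 2 × 2 = 8 cells if fully crossed (Participants). Spanish site at most 30; 130 screened per country; about 30% refusal (Recruitment strategy). About 14 per stratum within site, about 57 in total (Clinical measures).

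**Can the stated figures be reproduced?** I divided 400 by 4, 5, 6, 7, 8, 10 and 11 units, with 4 or 8 strata in each. Only 7 sites with 4 strata gives both figures:
- 400 / 7 = 57.1 per site, and 57 × 7 = 399
- 57.1 / 4 = 14.3 per stratum, and 14 × 4 = 56

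The figures may come from an older layout with 7 sites and 4 strata. That is an inference; the article does not say so.

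**What the stated figures would require in the stated design**
- 57 per site: 57 × 11 = 627 patients, 57% above 400. With Spain at its cap: 57 × 10 + 30 = 600.
- 14 in each of 8 cells: 14 × 8 = 112 per site, and 112 × 11 = 1,232 patients. With Spain at its cap: 112 × 10 + 30 = 1,150.
- The cap of 30 alone rules out 57 at the Spanish site.

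**What 400 patients allow**

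| Layout | Per site | Per cell, 8 strata | Per cell, 4 strata |
|---|---|---|---|
| 400 over 11 sites | 36.4 | 4.5 | 9.1 |
| Spain 30, 370 over 10 sites | 37 | 4.6 | 9.3 |

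The second row takes Spain to be one site, as the article's singular wording suggests.

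**Other readings of 57.** The sentence does not write per site after the number, so I tried the alternatives:
- Per country: 57 × 5 = 285, or 57 × 4 + 30 = 258.
- Pooled size of one stratum: 57 × 8 = 456, against 400 / 8 = 50 available.
- After 20% dropout: 400 × 0.8 = 320, and 320 / 11 = 29.1 per site. Inflated for dropout: 400 / 0.8 = 500, and 500 / 11 = 45.5.

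None fits.

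**Consistency of the country plan.** 4 × 130 × 0.70 + 30 = 394, within 1.5% of 400. The disagreement is therefore confined to the site and stratum figures.

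**Representativeness.** The article gives no stratum shares, so the inputs here are assumptions. For two age strata with share w of patients in the younger one and MetS proportions p1 (younger) and p2 (older), unweighted equal allocation estimates (p1 + p2)/2, while the population value is w·p1 + (1 − w)·p2.
- w = 0.5: no bias.
- w from 0.6 to 0.8, p1 = 25%, p2 = 40%: overstatement of 1.5 to 4.5 points.
- w from 0.6 to 0.8, p1 = 20%, p2 = 45%: overstatement of 2.5 to 7.5 points.

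This shows only that the bias depends on quantities the article does not give and can be zero.

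**The case against.** The best defence concedes the mismatch and argues that little depends on it. Most of that defence stands.

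- **Power.** A reader might infer that the ECS is underpowered. The calculation under Power and sample size compares patients with and without MetS across all 400 and uses no stratum or site size. With its stated 180/220 split, an effect size of 0.4 and a significance level of 0.002, power comes to 81.3%. (Whether that split agrees with the 31% stated beside it is a separate question.) What has no support is the claim that the stratum-by-site numbers ensure power.
- **Screening.** A reader might infer that recruitment will fall short. An expected 394 against 400, under a refusal rate given only as approximate, is no contradiction; at 29% refusal the total is 4 × 130 × 0.71 + 30 = 399.
- **Bias.** A reader might infer that MetS prevalence will be wrong. The Aims assign prevalence to registers, biobanks and medical records. The primary aim of the ECS is association among the five criteria. The stratum mix matters mainly for the descriptive distribution of the 32 combinations and less for associations within the sample.
- **Weights.** Their absence is no fault in a condensed article, because an analysis plan that is not shown may contain them. The objection is only to the statement that the quotas themselves secure representativeness.
- **Number of strata.** Eight is the natural reading of Participants, but 14 and 57 themselves imply four. The mismatch with 11 sites remains under either.

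**Conclusion.** The allocation sentence is wrong as written. Its figures contradict the number of sites, the total and the Spanish cap, and they also contradict the three-factor stratification if the factors are fully crossed. The stated 57 per site compares with an average of 36.4 (37 outside Spain). The stated 14 per cell compares with about 4.5 or 9.1. These averages assume equal site sizes, which the article does not promise; unequal sizes would not help, because 11 sites averaging 57 still need 627 patients.

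The assurance of representativeness does not follow from equal numbers per stratum unless the strata are equally large in the source population. The documents do not allow the size of that effect to be calculated.

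The documents do not support going further: the total of 400, the screening number and the stated power for the MetS comparison are untouched. The onset categories leave out onset at exactly 21 years, which is a minor gap.

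**What to change.** Reconcile Participants, Recruitment strategy and Clinical measures:

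1. Say whether there are 4 or 8 strata, that is, whether age of onset is crossed with age and sex.
2. Replace 14 and 57 with targets that sum to 400. As recruitment is planned by country, country quotas are the simplest: (400 − 30) / 4 = 92.5, so about 92 in each of the four larger countries, plus up to 30 in Spain. That is 92.5 / 8 = 11.6, or about 12 per cell per country with 8 strata, and 92.5 / 4 = 23.1 with 4. It also agrees with the expected yield of 130 × 0.70 = 91 per country.
3. Assign onset at exactly 21 to one of the two onset strata.
4. Remove the statement that these quotas ensure representativeness and power. Alternatively, support the representativeness part: log the number of eligible patients per stratum during selection, and weight the descriptive estimates by the inverse sampling fraction.

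Items 1 to 3 are text changes. The log in item 4 is a small task for sites, but it should start with selection, because the sampling fractions may not be recoverable later. Weighting costs some precision, depending on how unequal the strata are. If each of three independent factors is assumed to split 60/40, the design effect is 1.13 (effective sample size about 356 of 400); at 70/30 it is 1.56 (about 256). The loss applies only to the weighted descriptive estimates.
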